## Abstract

**Background:**

Local control rates in patients with retroperitoneal soft tissue sarcoma (RSTS) remain disappointing even after gross total resection, mainly because wide margins are not achievable in the majority of patients. In contrast to extremity sarcoma, postoperative radiation therapy (RT) has shown limited efficacy due to its limitations in achievable dose and coverage. Although Intraoperative Radiation Therapy (IORT) has been introduced in some centers to overcome the dose limitations and resulted in increased outcome, local failure rates are still high even if considerable treatment related toxicity is accepted. As postoperative administration of RT has some general disadvantages, neoadjuvant approaches could offer benefits in terms of dose escalation, target coverage and reduction of toxicity, especially if highly conformal techniques like intensity-modulated radiation therapy (IMRT) are considered.

**Methods/design:**

The trial is a prospective, one armed, single center phase I/II study investigating a combination of neoadjuvant dose-escalated IMRT (50–56 Gy) followed by surgery and IORT (10–12 Gy) in patients with at least marginally resectable RSTS. The primary objective is the local control rate after five years. Secondary endpoints are progression-free and overall survival, acute and late toxicity, surgical resectability and patterns of failure. The aim of accrual is 37 patients in the per-protocol population.

**Discussion:**

The present study evaluates combined neoadjuvant dose-escalated IMRT followed by surgery and IORT concerning its value for improved local control without markedly increased toxicity.

**Trial registration:**

NCT01566123

## Background

The retroperitoneal space is the site of origin for about 15% of soft tissue sarcomas
[1]. Complete excision with wide margins represents the mainstay of treatment, however even gross total resections are possible only in about 50% of the patients
[2,3] because of the often locally advanced tumors which frequently already involve vital structures at time of diagnosis
[3]. Even if gross total resection is possible, margins are typically narrow because of the normal tissue limitations
[3,4] consequently the local failure rate after surgery alone remains high
[5-7]. In accordance to extremity soft tissue sarcomas (STS), where randomized trials have demonstrated improved local control by the addition of radiation
[8,9], considerable interest has been paid in the use of postoperative radiation approaches in retroperitoneal STS also. However, the efficacy of postoperative external beam irradiation (EBRT) is limited because of the inability to deliver adequate doses in account for the tolerance limits of stomach, small bowel, kidney, liver and spinal cord
[10], especially when conventional radiation techniques are used. Because of the known dose-relationship resulting in improved local control rates if doses beyond 55–60 Gy are used
[11,12], some centers including ours investigated the use of an intraoperative radiation therapy (IORT) boost to overcome the dose limits of postoperative EBRT
[3,10,13-15]. The only randomized trial reported so far
[13] found a significantly improved local control rate of 60% using a combination of 20 Gy IORT and 35–40 Gy EBRT compared to 20% control with 50–55 Gy postoperative EBRT alone. The reduction of local failures was even accompanied by a lower rate of gastrointestinal toxicities with the use of IORT, but neuropathy emerged as a dose-limiting side effect.
[13]. However, it has been shown, that neurotoxicity is hardly increased if the intraoperative dose is limited to less than 15 Gy
[16]. Given the necessity of a slightly lowered intraoperative dose and the aim of a further improvement in local control, it seems reasonable to investigate an increased EBRT dose component in the combined treatment approach. Compared to the postoperative approach, preoperative radiation therapy and the use of improved irradiation techniques seem favourable for the following reasons : Preoperative radiation therapy allows for a more precise target volume definition and delineation with smaller safety margins, reduces toxicity to adjacent organs at risk because of their displacement through the tumor itself, may lead to a devitalisation of tumor cells including a down-sizing effect, and may avoid a treatment delay due to postoperative complications. Considering improved irradiation techniques, intensity-modulated radiation therapy (IMRT) has been shown to result in improved target coverage and reduced dose to adjacent organs at risk compared to conventional irradiation, as shown in several diseases including retroperitoneal sarcoma
[17,18], especially if complex shaped target volumes have to be treated
[19]. Further on, IMRT offers the opportunity to reduce overall treatment time using an integrated boost concept with simultaneously increased dose per fraction in parts of the target volume which are at increased risk for incomplete resection during planned surgery.

Therefore, the primary aim of this trial is to investigate the value of dose-escalated preoperative IMRT followed by surgery with an intraoperative electron boost to reduce the local recurrence rate without a markedly increased toxicity. This combination yields total doses which should be able to control even microscopic residual disease without harm to the adjacent organs at risk.

## Methods and design

### Study design

The trial is designed as a prospective single-center one-armed phase I/II study to assess the efficacy and safety of a combination regimen consisting of neoadjuvant intensity-modulated dose-escalated radiation therapy followed by surgery and an intraoperative electron radiation therapy boost to the tumor bed in patients with gross resectable or borderline resectable soft tissue sarcomas of the retroperitoneal space.

### Patient selection and inclusion/exclusion criteria

A minimum of 37 patients fulfilling the inclusion criteria listed below should be enrolled in this trial. Only patients meeting all of the inclusion criteria and missing all of the exclusion criteria (see Table
1) are considered for admission to the trial. Accrual will be stopped after the calculated sample size of the per-protocol population is reached (see statistical considerations).

**Table 1 T1:** Inclusion and exclusion criteria

**Inclusion criteria**	**Exclusion criteria**
written informed consent	missing written informed consent
histologically confirmed, primary or locally recurrent soft tissue sarcoma of the retroperitoneal space	missing histological conformation of soft tissue sarcoma
judged as at least marginally resectable	Desmoid Tumors (aggressive fibromatosis), Gastrointestinal Stroma Tumors (GIST)
absence of distant metastases	judged as gross incomplete or not resectable
tumor size ≥ 5 cm	incomplete staging
	presence of distant metastases
	prior radiation therapy to the abdominal region
	participation in another clinical interventional study
	inflammatory bowel disease

### Trial organization

The study has been designed by the Departments of Radiation Oncology and General Surgery of the University of Heidelberg in cooperation with the Departments of Radiation Oncology, Biostatistics and Medical Physics at the German Cancer Research Center (DKFZ) Heidelberg. It is carried out by the Department of Radiation Oncology at the German Cancer Research Center together with the Departments of Radiation Oncology and General Surgery at the University of Heidelberg. The trial is an investigator initiated trial.

### Coordination

The trial is coordinated by the Department of Radiation Oncology at the German Cancer Research Center (DKFZ) in cooperation with the Departments of General Surgery and Radiation Oncology of the University of Heidelberg. The Departments of Radiation Oncology at the German Cancer Research Center and at the University of Heidelberg are responsible for overall trial management, database management, quality assurance, reporting and for the scientific program of all trial related meetings. The trial has been registered at ClinicalTrials.gov [NCT01566123].

### Investigators

Patients will be recruited by the Departments of General Surgery, Radiation Oncology or Internal Medicine at the University Hospital of Heidelberg, the Department of Radiation Oncology at the German Cancer Research Center or the National Center for Tumor Diseases (NCT) at the University of Heidelberg. All investigators are experienced oncologists from the field of radiation oncology or surgery cooperating in this trial.

### Ethical and legal considerations

The study protocol was approved by the independent ethics committee of the Medical Faculty at the University of Heidelberg. The trial is carried out by adhering to local legal and regulatory requirements. The study complies with the Declaration of Helsinki 2004, the principles of Good clinical practice (GCP) and the German Federal Data Protection Act. Written informed consent is obtained from each patient before inclusion into the trial after nature, scope and possible consequences of participation in the trial have been explained by a physician.

### Study objectives and endpoints

The primary objective is the local control rate after 5 years. Secondary objectives are progression-free-survival, overall survival, acute and late toxicity, resectability and patterns of recurrence.

### Pretreatment evaluation

Initial work up consists of clinical examination, laboratory tests including renal and hepatic function, histological confirmation of diagnosis, CT or MR-imaging of the abdominal cavity, thoracic CT, bone scan, scintirenography, evaluation of general ability to receive major surgery and evaluation of resectability.

### Treatment assignment and schedule

All patients eligible for the trial after pre-treatment evaluation (see inclusion/exclusion criteria, Table
1) who gave written informed consent are registered in the trial and assigned to the same treatment regimen (see Figure
1). They receive immobilization and treatment planning examinations for neoadjuvant intensity-modulated radiation therapy (IMRT) either at the Department of Radiation Oncology at the German Cancer Research Center or the University of Heidelberg. Neoadjuvant intensity-modulated irradiation starts within 6 weeks after registration and is carried out in 5 fractions per week for 5–6 weeks using an image guided, stereotactic, intensity-modulated approach up to a total dose of 50–56 Gy. Reevaluation including restaging and assessment of toxicity takes place within 2 to 4 weeks after the last fraction. Surgical resection of the tumor including Intraoperative Radiation Therapy (IORT) with a single dose of 10–12 Gy is carried out within 6 weeks after the end of neoadjuvant irradiation at the Department Surgery in cooperation with the Department of Radiation Oncology at the University of Heidelberg. After postoperative recovery, all patients will be assigned to regular follow up visits either at the Department of Radiation Oncology at the German Cancer Research Center or at the Departments of Surgery or Radiation Oncology.

**Figure 1 F1:**
[figure not shown]
**Flow Chart of the Study.** IMRT: Intensity-Modulated Radiation Therapy, IORT: Intraoperative Radiation Therapy, Fx: Fractions.

### Neoadjuvant intensity-modulated radiation therapy and reevaluation

For external beam radiation therapy, patients are immobilized using a custom-made, individually manufactured body mask system (Scotch Cast^TM^, 3 M, St. Paul-Minneapolis, USA) or a vacuum pillow (BlueBag^TM^, Medical Intelligence, Schwabmünchen, Germany) combined with a custom-made individually manufactured head mask system (Scotch Cast^TM^, 3 M, St. Paul-Minneapolis, USA) mounted to a stereotactic body frame, resulting in an accuracy of less than 3.6 mm
[20]. For treatment planning, contrast enhanced CT as well as MR imaging is performed for optimal target definition. Organs at risk like small bowel, stomach, liver, kidneys, bladder, femoral heads and spinal cord are contoured. The Gross Tumor Volume (GTV) includes all macroscopically visible tumor lesions on imaging. The clinical target volume (CTV) includes the gross tumor volume with a safety margin of 1.5 cm in all directions. A safety margin of 5 mm is added to obtain the Planning Target Volume (PTV). The margins may be reduced with respect to anatomical borders or organs at risk at the discretion of the investigator. The prescribed dose to the PTV is 45–50 Gy in single fractions of 1.8-2.0 Gy. The prescribed dose to the GTV is 50–56 Gy in single fractions of 2.0-2.4 Gy using an integrated boost concept. The total dose is prescribed to the median of the GTV, while the target volumes should be surrounded by the corresponding 95% isodose lines. The generally accepted tolerance doses
[21] for the organs at risk are maintained during the radiation therapy planning. Inverse treatment planning is carried out using the planning systems at the Department of Radiation Oncology of the German Cancer Research Center. Treatment is performed using step-and-shoot intensity modulated radiation therapy with 5 to 13 coplanar 6 MV-beams after stereotactic target point localisation. Setup correction is done using an image-guided approach with an In-Room-CT on rails (Siemens Somatom Emotion, Siemens, Erlangen, Germany) by comparison of the current CT with the planning CT at least once a week. Reevaluation including restaging with abdominal CT or MRI and assessment of toxicity is performed 2 to 4 weeks after the last fraction of neoadjuvant irradiation.

### Surgery and intraoperative radiation therapy

Surgery is performed within six weeks after completion of neoadjuvant irradiation at the Department of General Surgery of the University of Heidelberg. A gross total resection is attempted. An additional intraoperative electron boost will be performed using a dedicated linear accelerator inside the operation theatre (Siemens Mevatron, Siemens, Concord, USA). The target volume of the intraoperative boost includes the tumor bed or the high risk region for positive or close margins as defined by the treating surgeon and the radiation oncologist together if the complete tumor bed cannot be covered. Therefore an applicator of appropriate size is placed inside the abdominal cavity and attached to the table. Uninvolved radiosensitive tissues are removed from the treatment area or covered by lead shielding. After alignment with the accelerator, the target volume is irradiated with a single dose of 10–12 Gy, prescribed to the 90% isodose. The electron energy is selected according to the tissue depth that has to be covered in order to encompass the target volume with the 90% isodose.

### Follow up

Regular follow up visits start at the day of discharge from the Department of General Surgery at the University of Heidelberg and will take place every 3 months after surgery for the first 2 years and every 6 months for three further years. They will include clinical and laboratory examinations, CT or MR-imaging of the abdominal cavity, thoracic CT (every 6 months in the first two years, every year thereafter) and assessment of acute and late toxicity as well as any other necessary examination, test or imaging in case of suspicion of local or distant failure at discretion of the treating physician. All patients will be followed for 5 years or until death or end of study participation due to other reasons.

### Analysis populations

#### Full analysis set

The Full analysis Set (FAS) consists of all patients included in the trial irrespective whether any protocol violation was present during treatment under study conditions or whether the patient was taken off-study any time after treatment start, except patients who withdraw informed consent before the first radiation treatment or about whom it becomes known that major in-/exclusion criteria have been violated which would have excluded them from study participation when known at start of treatment.

#### Per protocol population

The Per Protocol population consists of all patients meeting the inclusion criteria and receiving the full treatment according to this protocol.

### Assessment of efficiacy

Local control rate after 5 years is the primary endpoint of the trial. It will be assessed by repeated CT or MR-imaging during regular follow up. In case of a single suspicious locoregional lesion, histological confirmation will be attempted. Otherwise, new lesions with typical radiological signs and/or clinical behaviour of a local recurrence will be counted as local recurrence. In case of missing surgical resection of the tumor after neoadjuvant radiotherapy, a local disease progression according to RECIST criteria (version 1.0) will be counted as a local recurrence. Special attention should further be given to avoid that tissue reaction to radiation or surgical treatment is classified as local recurrence or disease progression. Variations in post-radiotherapy or post-surgery imaging may continue for months and may be accompanied by clinical signs and symptoms. In such cases, the labelling of the lesion suspicious for recurrence or progression must be based on the clinical follow-up including their developement over time. If the course of events shows that true recurrence or progression indeed occurred, the date of the first appearance or progression of the suspicious lesion is to be considered as the date of recurrence or progression.

Progression-free survival (PFS) is a secondary endpoint of the study, determined as the time span from the first day of radiation therapy until local or distant recurrence or progression or death due to any cause is found, whatever occurred first. Patients alive without progressive disease at the time of data analysis will be censored at the time of the most recent follow up. In case of lesions suspicious for distant metastases, histological or cytological confirmation is attempted. Otherwise, new lesions with typical radiological signs and/or clinical behaviour of distant metastases will be counted as progression.

Overall survival is a secondary endpoint of the study, calculated from the first day of radiation treatment until death of any cause. Patients not reported dead or lost to follow-up will be censored at the date of the last follow-up examination.

### Assessment of toxicity

Acute radiation toxicity will be assessed according to Common Terminology Criteria for Adverse Events Version 3.0 (CTCAE 3.0) during the time period from the first day of neoadjuvant radiation treatment until 3 months after surgery. Late radiation toxicity will be scored according to CTCAE 3.0 and RTOG criteria. Toxicity will regularly be evaluated by clinical and laboratory examinations at least once a week during neoadjuvant external beam radiation therapy and the first follow up visits at discharge of the Department of General Surgery and after 3 months. Late toxicity will regularly be scored during every further regular follow up visit.

### Sample size estimation, confirmatory and descriptive analyses

The primary endpoint of the trial is the local control rate after five years (LC-5yR). The study is designed to demonstrate that the combination of neoadjuvant dose-escalated intensity-modulated radiation therapy with surgery and intraoperative radiation therapy can improve the local control rate after five years. Local control rate after five years in a comparable patient population treated with standard procedures (surgery followed by adjuvant three-dimensional conformal radiotherapy) was estimated to be 50% according to the literature. The sample size calculation was designed on the assumption to detect an improvement by 20% in this primary endpoint. For sample size calculation, the following hypotheses have been made:

p0 is the largest LC-5yR which, if true, implies that the efficacy of the study treatment is too low. In the present trial P0 has been taken as 50%

p1 is the lowest LC-5yR which, if true, implies that the efficacy of the treatment is adequate. In the present trial p1 has been taken as 70%

α is the acceptance probability of considering adequate efficacy of the treatment with a true LC-5yR equal or lower to p0 (false positive decision). In the present trial α has been taken as 5%

β is the acceptance probability of rejecting adequate efficacy of the study treatment with a true LC-5yR at least equal to p1 (false negative decision). In the present trial β has been taken as 20%.

Using the one-sided binomial test (“Exact Test”) with the given hypotheses, the study requires 37 patients to decide whether the LC-5yR is less or equal to 0.5 or greater or equal to 0.7. If the number of locally controlled patients is ≥24, the hypothesis that LC-5yR is ≤ 0.5 will be rejected with a target error rate of 0.05. Sample size calculation and confirmatory analysis are based on the per protocol population
[22].

Secondary endpoints are all of explorative nature and reported using descriptive analysis methods. Time to event data (progression free survival, overall survival) will be evaluated using the Kaplan-Meier-Method.

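### The count rule of 24 out of 37 delivers its stated 5% alpha and 80% power for local control only if every patient's local status at five years is known, and the protocol foresees that it will not be

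*Protocol article*

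**What the plan says.** All places are in the Protocol article.

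- **Sample size estimation, confirmatory and descriptive analyses.** The primary endpoint is the local control rate after five years, with p0 = 50%, p1 = 70%, alpha = 5% and beta = 20%. An exact one-sided binomial test in 37 patients is prescribed. The success condition is a count: "If the number of locally controlled patients is ≥24". Sample size and confirmatory analysis both rest on the per-protocol population.
- **Same section, on the secondary endpoints.** "Time to event data (progression free survival, overall survival) will be evaluated using the Kaplan-Meier-Method". Local control is not in that list.
- **Follow up.** "All patients will be followed for 5 years or until death or end of study participation due to other reasons".
- **Per protocol population.** Membership depends on eligibility and on receiving the full treatment. Completing five years of follow-up is not required.
- **Patient selection and inclusion/exclusion criteria.** Accrual stops once the calculated per-protocol number is reached. No allowance for incomplete follow-up is mentioned.
- **Assessment of efficacy.** This section defines local recurrence and its date, and gives censoring rules for progression-free and overall survival. It does not say how to count a patient who dies or leaves without local recurrence before five years.

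**The concern.** A binomial count needs each of the 37 patients to be either controlled or not controlled at five years. A patient who dies of distant metastases at two years with no local recurrence is neither, and the same holds for one who withdraws at three years. The protocol recognises incomplete observation for its secondary time-to-event endpoints, yet fixes the primary test in a form that has no place for it.

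This is the trial's only confirmatory decision. With identical data on local recurrence, the verdict could turn on how a few early deaths are counted.

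**Working it through.** **1. The plan's own figure.** With X the number controlled among 37:

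- P(X ≥ 24 | p = 0.50) = 0.0494
- P(X ≥ 24 | p = 0.70) = 0.8071
- A cut-off of 23 would give alpha 0.0939, so 24 is correct.

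The stated n, cut-off, alpha and power are reproduced when all 37 statuses are known.

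**2. Inputs for incomplete follow-up.**

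- From the protocol: n = 37, cut-off 24, and five-year local control L = 0.50 or 0.70.
- Assumed, because the documents give no figure: a probability q of death or loss by five years in the absence of local recurrence, with q = 5%, 10%, 20% or 30%.
- Also assumed: exponential times, independent of local recurrence, and 50% and 70% read as freedom from local failure in the absence of death or loss.

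**3. Formulas.** λL = −ln(L)/5 and λD = −ln(1 − q)/5.

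- Under observation and controlled at five years: A = L(1 − q)
- Observed local recurrence: R = λL/(λL + λD) × (1 − A)
- Counted as controlled if early deaths and losses are successes: 1 − R
- Counted as controlled if they are failures: A

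Example with L = 0.50 and q = 10%: λL = 0.1386, λD = 0.0211, A = 0.45, R = 0.868 × 0.55 = 0.477. Success coding then gives 1 − R = 0.523, and P(X ≥ 24 | 0.523) = 0.084.

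**4. Results for the rule of at least 24 out of 37.**

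| q | Success coding: apparent rate when true rate is 50% | Alpha | Failure coding: apparent rate when true rate is 70% | Power | Alpha under failure coding |
|---|---|---|---|---|---|
| 0% | 0.500 | 0.049 | 0.700 | 0.81 | 0.049 |
| 5% | 0.511 | 0.065 | 0.665 | 0.66 | 0.025 |
| 10% | 0.523 | 0.084 | 0.630 | 0.48 | 0.012 |
| 20% | 0.546 | 0.138 | 0.560 | 0.18 | 0.002 |
| 30% | 0.571 | 0.216 | 0.490 | 0.04 | 0.0002 |

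**5. Exclusion.** The expected number evaluable is 37(A + R). At q = 20% this is 31.6 (true 50%) or 30.7 (true 70%), so a cut-off derived for 37 no longer applies. The expected proportion A/(A + R) is also biased downwards: 0.468 for a true 0.50 and 0.674 for a true 0.70.

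**6. Kaplan-Meier alternative at n = 37.** This was simulated (20,000 runs) with the same independent exponential times. Success means that the one-sided 95% lower log-log bound at five years exceeds 50%.

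| q | Alpha | Power at 70% |
|---|---|---|
| 0% | 0.049 | 0.81 |
| 10% | 0.038 | 0.74 |
| 20% | 0.039 | 0.72 |
| 30% | 0.040 | 0.68 |
| 50% | about 0.04 | 0.60 |

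These alphas depend on independence. With an assumed correlation of 0.5 between the latent times to death and to local failure (Gaussian copula), alpha at q = 30% is about 0.10, and a true 50% is estimated at about 54%.

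**The case against.** **The count test can be kept valid.** A reader might infer that no way of counting early deaths makes the test valid. That goes too far. Counting them as failures holds alpha below 5% at every rate examined. What remains is that this coding answers a different question (alive, under observation and locally controlled) and that the 80% power for local control is lost.

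**This is a coding rule for the full protocol or analysis plan.** Such rules are commonly left there, and the article adopts none of the codings above. It also does not rule out time-to-event methods for local control: the Kaplan-Meier sentence concerns secondary endpoints, and a date of recurrence is defined. This narrows the point without removing it. The article itself fixes the test, the denominator, the cut-off and both error rates, and none of the three codings examined preserves them together.

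**The size rests on assumed death rates.** True. A reader might take the 22% false-positive rate at q = 30% as the trial's actual rate, and the documents do not support that. At q = 5% the inflation is only to 6.5%. Even there, though, power under failure coding is 0.66 rather than 0.80.

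**Kaplan-Meier has its own weakness, and cumulative incidence is equally defensible.** The first part stands: censoring deaths protects alpha only if death and loss are independent of local failure. On the second, a cumulative-incidence primary is possible but would need p0 and p1 restated. One minus the cumulative incidence is the quantity 1 − R, which is 0.571 at q = 30% when control in the absence of death is 50%.

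**Conclusion.** The point holds in a limited form. The derivation of 37 and 24 is correct. The fault is that a fixed count is used for an endpoint whose status will be unknown at five years for anyone who dies or leaves recurrence-free. Once that happens, the stated alpha of 5% and power of 80% for local control cannot both be relied on. Success coding takes alpha to between 0.065 and 0.216, and failure coding takes power to between 0.66 and 0.04, for assumed rates from 5% to 30%. Exclusion removes the basis of the cut-off.

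The direction does not depend on the particular rate, but the size does. The figures also assume independent exponential times, and that the 50% benchmark means freedom from local failure in the absence of death, which the protocol does not spell out. The documents do not support saying that alpha fails under every coding, or that Kaplan-Meier guarantees alpha.

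**What to change.** Replace the count rule with a time-to-event primary analysis:

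1. Estimate freedom from local failure at 60 months by Kaplan-Meier, counted from the first day of radiation therapy (the origin already used for progression-free and overall survival). Censor recurrence-free deaths and losses.
2. Declare success if the one-sided 95% lower log-log bound exceeds 50%.
3. Report the cumulative incidence of local failure, with death as a competing event, alongside it.
4. State that the Kaplan-Meier analysis assumes death and loss to be independent of local failure, and that alpha can exceed 5% if they are positively correlated.
5. Keep n = 37 and restate the power as below 80%: under independence about 0.74, 0.68 and 0.60 at 10%, 30% and 50% early death or loss.

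No new data are needed, since imaging and recurrence dates are already collected. The cost is the less favourable power figure. Holding to the protocol's own 80% target under incomplete follow-up would require more than 37 patients, so accepting the lower power should be an explicit decision by the sponsor.

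### The confirmatory test is run on completers only, so local failures before surgery, which the endpoint definition counts, can never enter it

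*Protocol article*

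**What the plan says.** Four statements in the protocol article bear on this point.

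- **Test population** (Sample size estimation, confirmatory and descriptive analyses): "Sample size calculation and confirmatory analysis are based on the per protocol population". The test is a one-sided exact binomial with p0 = 50%, p1 = 70%, α = 5% and β = 20%. It needs 37 patients and declares success at 24 or more locally controlled.
- **Who is in it** (Per protocol population): "The Per Protocol population consists of all patients meeting the inclusion criteria and receiving the full treatment according to this protocol". Under Treatment assignment and schedule, the treatment is neoadjuvant IMRT followed by "Surgical resection of the tumor including Intraoperative Radiation Therapy (IORT) with a single dose of 10–12 Gy". The section on surgery and intraoperative radiation therapy describes the same sequence.
- **What counts as failure** (Assessment of efficiacy): "In case of missing surgical resection of the tumor after neoadjuvant radiotherapy", then "a local disease progression according to RECIST criteria (version 1.0) will be counted as a local recurrence".
- **Accrual** (Patient selection and inclusion/exclusion criteria): enrolment ends once the calculated per-protocol number is reached, so patients outside that set are in effect replaced.

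A full analysis set (FAS) is defined that would keep patients despite protocol deviations or early discontinuation. The article gives it no role in the confirmatory test.

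**The concern.** The endpoint definition foresees a patient who has IMRT, is not resected and progresses locally, and it says that this is a local recurrence. The per-protocol definition removes the same patient because the full treatment was not given. The rule can therefore never add a failure to the count that decides the trial.

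Membership of the tested set is settled after treatment starts, partly by events that are failures under the protocol's own definition. Loss of resectability before surgery is a risk of the neoadjuvant sequence. Eligibility requires only that a tumour be judged at least marginally resectable, and restaging falls between IMRT and surgery. At stake is whether a positive result describes the regimen as started or only the patients who completed it.

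**Working it through.** **1. The plan's own figure.** Inputs from the sample size section: n = 37, critical number 24, p0 = 0.50, p1 = 0.70.

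- P(X ≥ 24 | 37, 0.50) = 0.0494
- P(X ≥ 24 | 37, 0.70) = 0.807

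n = 37 is the smallest size with exact α ≤ 5% and power ≥ 80% (n = 36 gives 73.7%, n = 35 gives 77.3%). The calculation is right for a binomial sample without selection. The question is which patients form that sample.

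**2. Effect of selection.** The documents give neither the share f of treated patients who fall outside the per-protocol set nor the proportion g of them who fail locally. Both are assumed here. Assume also that 50% is the true local control rate among all treated patients. Then

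0.50 = (1 − f) × PP rate + f × (1 − g), so PP rate = (0.50 − f(1 − g)) / (1 − f).

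Example: f = 0.10, g = 0.75 gives (0.50 − 0.025)/0.90 = 52.8%, and P(X ≥ 24 | 37, 0.528) = 9.5%.

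Probability that ≥24/37 is reached although control among all treated is 50%:

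| Non-completers (f) | g = 50% | g = 75% | g = 100% (worst case) |
|---|---|---|---|
| 5% | 4.9% | 6.8% | 9.2% |
| 10% | 4.9% | 9.5% | 16.5% |
| 15% | 4.9% | 13.3% | 28.4% |
| 20% | 4.9% | 18.7% | 45.5% |

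In the worst-case column the per-protocol rates are 52.6, 55.6, 58.8 and 62.5%. At g = 50% exclusion is unrelated to outcome and there is no bias.

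**3. A check that needs no rate.** Take the borderline success, 24/37 (one-sided p = 0.049), and add back excluded local failures:

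- one: 24/38, p = 0.072
- two: 24/39, p = 0.100
- four: 24/41, p = 0.174

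A single excluded failure reverses a borderline result.

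**4. The test on the FAS.** Critical number from the exact binomial at p0 = 0.50:

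| FAS size | Critical number | α | Power at 70% |
|---|---|---|---|
| 38 | 25 | 3.6% | 77.4% |
| 40 | 26 | 4.0% | 80.7% |
| 41 | 27 | 3.0% | 77.6% |
| 42 | 27 | 4.4% | 83.6% |

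If 70% was meant for completers only and 10% do not complete and all fail, the FAS rate is 0.90 × 0.70 = 63%. Reaching 37 completers takes 37/0.90 ≈ 42 patients, and ≥27/42 then has power of about 50%.

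**The case against.** **The benchmark.** The sample size section takes 50% from patients given surgery followed by adjuvant three-dimensional conformal radiotherapy. As worded, these patients had surgery. If p0 is a rate in operated patients, completers are the closer comparison on resection, and the test keeps its 4.9% level for that question. Scoring unresected patients as failures against such a p0 would err the other way. With completer control of 50% and 10% non-completers all failing, the FAS rate is 0.90 × 0.50 = 45%, and ≥27/42 is reached with probability of only about 0.9%. This stands. A reader might infer from the table that the true type I error is 16% or 45%. The documents do not support that, because those figures need 50% to be the null for all treated patients and every non-completer to fail locally.

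**Not every non-completer is a failure.** The endpoint rule counts local progression without resection, not non-completion. A reader might infer that stopping for toxicity, distant metastases at restaging, or resection without IORT are failures removed because of their outcome. The rule does not say so, and such patients dilute the bias. This stands too, and is why the 75% and 50% columns are shown.

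**The risk is still reported.** Resectability and patterns of recurrence are secondary endpoints, PFS runs from the first day of radiation, and the per-protocol choice is openly prespecified. The failures are not hidden, but none of this brings them into the confirmatory test.

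**Eligibility exclusions from the FAS.** The FAS also drops patients "about whom it becomes known that major in-/exclusion criteria have been violated", which a reader might take as a second route for removing failures. The same sentence limits this to violations that would have barred entry if known at the start of treatment, so no further restriction is needed.

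**Conclusion.** The point holds as a conflict between the endpoint definition and the analysis population. Unresected local progressors are failures by definition, yet they cannot be counted in the confirmatory test and are replaced. This rests on reading full treatment as IMRT, resection and IORT, which the treatment sections support, and the article offers no other reading.

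The direction is upward whenever excluded patients fail locally more often than completers. The size cannot be fixed from the documents. Under a 50% null for all treated patients and 5 to 20% non-completion, the false-success probability runs from 4.9% (no association with outcome) through 6.8 to 18.7% (75% fail) to 9.2 to 45.5% (all fail). If the 50% benchmark is itself conditional on surgery, it does not define an error rate for the whole strategy, and the article does not say which is meant. In either case the primary conclusion can turn on one excluded patient, so this should be settled before the confirmatory analysis.

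**What to change.** 1. Make the FAS, taken as patients who started IMRT, the confirmatory set. Apply the existing rule for unresected patients and keep the per-protocol result as supportive.
2. State which population p0 = 50% and p1 = 70% describe, and restate the power for the FAS.
3. State that the critical number comes from the exact binomial for the FAS size reached, for example ≥26 of 40 (α 4.0%, power 80.7% at 70%) or ≥27 of 42 (α 4.4%, power 83.6%).
4. Align the accrual wording. Stopping at 37 per-protocol patients leaves the FAS size to chance, and at some sizes (38 or 41, for example) power at 70% is below 80%.
5. State that unresected patients follow the same imaging schedule. The Follow up section starts visits at surgical discharge and times them from surgery, so it sets no schedule for them.
6. Confirm how an unresected patient without progression is scored. As written, the rule would not count that patient as a recurrence.

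**Cost.** This is a protocol amendment that changes the accrual rule as well as the analysis wording, and perhaps a few more patients. Early failures will count against the regimen. If 70% was meant for completers only, the loss of power is serious: about 50% at a FAS rate of 63% with n = 42, and about 93 patients (≥55 controlled) would be needed to restore 80%.
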